## Abstract

**Introduction:**

Progesterone-primed cycles effectively suppress the pituitary LH surge during ovarian stimulation in oocyte donors and in the infertile population. Particularly in oocyte donors, the use of synthetic progesterone (progestins) has been explored in prospective clinical trials, showing mixed results. This trial was designed to determine whether the use of micronized natural progesterone is as effective as the GnRH-antagonist protocol in terms of the number of mature oocytes (MII) retrieved in oocyte donation cycles as a primary outcome, and it also aims to explore the corresponding results in recipients as a secondary outcome.

**Methods:**

We propose a prospective, open-label, non-inferiority clinical trial to compare a novel approach for oocyte donors with a control group, which follows the standard ovarian stimulation protocol used in our institution. A total of 150 donors (75 in each group) will be recruited and randomized using a computer algorithm. After obtaining informed consent, participants will be randomly assigned to one of two ovarian stimulation protocols: either the standard GnRH antagonist or the oral micronized natural progesterone protocol. Both groups will receive recombinant gonadotropins tailored to their antral follicle count and prior donation experiences, if any. The primary outcome is the number of mature metaphase II (MII) oocytes. Secondary measures include treatment duration, pregnancy outcomes in recipients, as well as the economic cost per MII oocyte obtained in each treatment regimen. Analyses for the primary outcome will be conducted in both the intention-to-treat (ITT) and per-protocol (PP) populations. Each donor can participate only once during the recruitment period. The estimated duration of the study is six months for the primary outcome and 15 months for the secondary outcomes.

**Discussion:**

The outcomes of this trial have the potential to inform evidence-based adjustments in the management of ovarian stimulation protocols for oocyte donors.

**Clinical trial registration:**

ClinicalTrials.gov, identifier, NCT05954962.

## Highlights

• First randomized controlled study comparing the effectiveness of micronized natural progesterone (Seidigestan®) with the GnRH-antagonist protocol in terms of the number of mature oocytes (MII) retrieved in oocyte donation cycles. The primary outcome focuses on this comparison, with a secondary aim of exploring corresponding results in recipients.• The trial is designed with several strengths, including a randomized and controlled structure to minimize bias. Furthermore, its double-center approach enhances the generalizability of the results. The use of fresh blastocyst-stage embryo transfers will provide an opportunity for a secondary examination of both embryo quality and the ongoing pregnancy rate in recipients.• The outcomes of this trial carry the potential to significantly influence the field by providing evidence-based insights. Successful results could lead to adjustments in the management of ovarian stimulation protocols for oocyte donors.

## Introduction

The advent of controlled ovarian stimulation dates back to the 1980s when gonadotropins and clomiphene citrate were initially employed. However, this approach often led to the occurrence of endogenous LH surges in up to 50% of cases (1). Such LH surges triggered ovulation, resulting in a subsequent rise in serum progesterone levels, making it impossible to proceed with the necessary oocyte retrieval for *in vitro* fertilization.

To address this issue, GnRH agonists were introduced in the 1980s (2). These agonists, despite causing an initial and transient surge in both FSH and LH (known as the flare-up effect), eventually led to the suppression of pituitary GnRH receptor secretion (3). This breakthrough allowed for the recruitment of a greater number of follicles without the risk of premature luteinization, thereby improving the success rates of *in vitro* fertilization and enabling the scheduling of stimulation cycles (4). However, the use of GnRH agonists came with trade-offs, including higher exogenous gonadotropin expenses due to the lack of endogenous secretion, longer stimulation periods, and the requirement for the final oocyte maturation trigger using human chorionic gonadotropin.

The solution to these drawbacks came with the discovery of the third generation of GnRH antagonists, such as Cetrorelix and Ganirelix, which did not carry the risk of anaphylactic reactions seen in previous generations (5). These compounds allowed for the suppression of pituitary gonadotropin production in a reversible manner. For instance, discontinuing the administration of Ganirelix at a dose of 0.25 mg resulted in the complete disappearance of its effects within 24-27 hours (6). As a result, they enabled shorter stimulation periods (requiring lower doses of exogenous gonadotropins), reduced costs, and also facilitated the use of GnRH agonists with their flare-up effect for oocyte trigger, leading to a significant decrease in overall rates of ovarian hyperstimulation syndrome (7).

In 2015, the use of progestogens to suppress the LH surge in the follicular phase was first published, offering a cost-effective alternative to antagonists in ovarian stimulation (8). This approach also simplified the process by transitioning from subcutaneously administered antagonists to orally administered medications. Subsequently, three randomized clinical trials have been published, demonstrating the effectiveness of continuous use of dydrogesterone (9) and medroxyprogesterone acetate or MPA (10, 11) as progestogens capable of inhibiting the LH surge.

To date, there has been no randomized study comparing the use of micronized natural progesterone (MNP) to the current standard treatment, namely, the antagonist protocol. We have retrospective data suggesting its similarity to treatment with MPA (12) in terms of the number of oocytes retrieved, as well as prospective data indicating its non-inferiority compared to dydrogesterone (13). This study represents the first randomized trial comparing Seidigestan® as MNP to the antagonist protocol.

## Outcomes

The primary objective of this study is to compare the efficacy (non-inferiority) of the MNP protocol (Seidigestan®) to an antagonist protocol, using the number of mature metaphase II (MII) oocytes as the primary outcome variable.

Our secondary objectives are detailed in **Table 1**.

**Table 1 T1:** Secondary outcomes for comparison of oral progesterone vs GnRH antagonist.

Treatment	Analyzing and comparing the baseline characteristics of each group of donors
	Comparing the gonadotrophin dose and treatment duration
Laboratory	Fertilization rate per-oocyte injected
	Assessing whether there are differences in the performance of these MII oocytes in fresh cycles and their potential to develop into blastocysts after ICSI
Clinical	Documenting the fresh transfers of blastocysts originating from each protocol and the endometrial preparation protocols
	Biochemical pregnancy: a pregnancy diagnosed only by the detection of beta hCG in serum or urine, which fails to progress to the point of ultrasound confirmation
	Clinical pregnancy: an intrauterine pregnancy diagnosed by ultrasonography
	Ongoing pregnancy: the presence of a heartbeat as seen by ultrasonography 12 weeks gestation
	Multiple pregnancy: two or more gestational sacs seen by ultrasonography
	Early pregnancy loss: the spontaneous loss of an intrauterine pregnancy, where there is no fetal heartbeat detected at the time of ultrasound at 6–8 weeks
	Ectopic pregnancy: a pregnancy outside the uterine cavity, diagnosed by ultrasound, surgical visualization or histopathology
	Miscarriage: the spontaneous loss of an intrauterine pregnancy with fetal heartbeat prior to 20 completed weeks of gestational age
	Live birth: the complete expulsion or extraction from a woman of a product of fertilization, after 22 completed weeks of gestational age; which, after such separation, breathes or shows any other evidence of life, such as heartbeat, umbilical cord pulsation or definite movement of voluntary muscles, irrespective of whether the umbilical cord has been cut or the placenta is attached
	Analyzing possible obstetric differences between both protocols
Cost-effectiveness	Contrasting the economic cost per number of mature oocytes (MII) obtained in each treatment regimen
Quality of life	Women will also be asked to complete a survey consisting of questions related to treatment tolerability

## Materials and methods

### Study design

To address both the overarching and specific objectives, we have designed a prospective, randomized, non-inferiority comparative clinical trial, conducted in an open-label fashion, with a control group following the standard therapeutic protocol at our institution for ovarian stimulation in oocyte donors during the year 2023. This multicenter study involves the locations in Alicante and Elche, which are part of IB S.L. (Instituto Bernabeu S. L), as well as the gynecology center Accuna (Namsomara S.L). The observer (the gynecologist conducting the ultrasound) will be blinded to the patient’s group allocation, and the person responsible for data analysis will also be blinded to group assignment. The blinding may be removed if the physician responsible for the subject deems it necessary for safety reasons. **Figure 1**.

**Figure 1 f1:**
[figure not shown]
Study flow diagram.

#### Oocyte donors and ovarian stimulation

After concluding the suitability assessment processes, potential oocyte donors will be approached for their willingness to participate in the study. They will be provided with an explanation of the study and presented with the informed consent form and patient information sheet. Random allocation has been executed using the SPSS Statistics macro!RNDSEQ (Domenech JM. Generation of Random Sequences [computer program]. V2011.09.09. Bellaterra: Universitat Autònoma de Barcelona; 2011), ensuring that both study groups have an equal likelihood of assignment at each instance. The researchers will not have access to the randomization list. The designated individual responsible for randomization will open each patient’s randomization envelope (which is opaque) and allocate the corresponding medication (Seidigestan® oral vs. Ganirelix subcutaneous). Patients will not be blinded to their assigned group due to the differing routes of medication administration, and neither will the randomization administrator nor the nursing staff. Participants in this study will not receive any specific additional financial compensation.

The patient will notify the clinic on the first day of her menstrual cycle and will be scheduled for an appointment during the initial four days of her cycle. During this visit, an ultrasound examination will be conducted to ensure there are no contraindications to commence ovarian stimulation. If no contraindications are found, the administration of the prescribed dose of gonadotropin (Bemfola®) will commence, and this day will be considered the first day of stimulation. The gonadotropin starting dose was selected to balance follicular recruitment optimization and minimize the risk of high response. To summarize, the suggested optimal dose was 150 IU for donors with an antral follicle count (AFC) greater than 14, while a dose of 225 IU was deemed suitable for donors with 10-14 antral follicles. In cases where fewer than 10 follicles were observed, a dose of 300 IU was determined. It’s important to note that, in line with clinician discretion, these doses could be adjusted based on the donor’s BMI, and responses to previous stimulations (when appropriate).

If the donor has been on oral contraceptive pills (OCPs) in the previous month, she will be scheduled for a baseline ultrasound examination (Visit 1) between 5-7 days after discontinuing the OCPs. Ovarian stimulation will commence on this day.

*For the study group*, starting on this day, they will begin taking one 200 mg soft capsule of Seidigestan® in the evening, a regimen that will continue until the day of the GnRH agonist (Decapeptyl® 0.4 mg). At this point, a blood sample will be collected for subsequent analysis of baseline hormone levels (LH, estradiol, and progesterone) **Table 2**.

**Table 2 T2:** Overview of study visits.

	Enrollment / Baseline	COS phase	GnRH agonist trigger	OPU	Follow-up OPU + 3 days
Information and counselling	X				
Signing of informed consent	X				
Treatment related data collection	X	X	X	X	X
Randomization	X				
Transvaginal ultrasound scan	X	X	X		
Blood sample	X	X	X		

*Both groups* will be scheduled for a follow-up ultrasound and blood analysis on day 5-6 of stimulation. *For participants in the control group*, the nurse will instruct them on the initiation of the GnRH antagonist (Ganirelix. Astarté® 0.25 mg) according to a fixed day 5/6 protocol. This regimen will be maintained until the day of administration of the GnRH agonist (Decapeptyl® 0.4 mg) to trigger final oocyte maturation. During ovarian stimulation controls, doctors in charge of subjects have freedom to change gonadotropin dosage if needed.

In the event that more than 26 hours have elapsed since the last Ganirelix injection until the time of agonist administration, the patient will be advised to administer an additional dose of Ganirelix due to the risk of falling below the minimum effective blood concentration (6). This additional dose should be administered at least 7 hours before the scheduled time for the analog administration (14).

Following this, participants will be scheduled for follow-up ultrasound and blood analyses every 24-72 hours as determined by the medical team.

Ovarian stimulation will be deemed complete when more than 6 follicles of equal or greater than 18 mm in size are observed. On the same day, the final oocyte maturation will be triggered by administering 0.4 mg of triptorelin acetate (Decapeptyl® 4 ampoules), the final study blood sample will be obtained, and the oocyte retrieval will be scheduled 36 hours later, following the center’s standard protocol.

At each visit, participants will be asked about the occurrence of any adverse effects or new symptoms, as well as any concurrent medication they may be taking. Moreover, participants will return used injectables and given blisters of oral progesterone in each consultation to monitor compliance with the protocol.

Ovarian stimulation will be discontinued in the event of poor response (*i.e.* ≤ 8 follicles ≥ 14 mm), and consequently, the administration of any medication will cease if the criteria for final oocyte maturation are not met within a maximum of 14 days from the initial gonadotropin dose administration.

The final visit will involve a telephone call conducted 72 hours after the oocyte retrieval to gather information regarding any surgical or stimulation-related complications.

Our donor program ensures a minimum of 8 metaphase II oocytes per recipient. Therefore, cumulus-corona-oocyte complexes (CCOs) are decumulated on the day of the donor’s oocyte retrieval and fertilized using intracytoplasmic sperm injection (ICSI). Only in exceptional cases, as determined by medical judgment, where conventional IVF may be more beneficial, will the decumulation process not be performed. All embryo transfers will occur at the blastocyst stage.

### Blood sample collection during the trial

Blood samples will be drawn during trial visits that include vaginal ultrasounds. These samples will be analyzed for estradiol, progesterone, and LH levels.

#### Recipients and endometrial preparation

Recipients will be between 18 and 50 years old at the time of embryo generation with different indications to receive donor oocytes: advanced maternal age, failed IVF cycles with own oocytes, failed insemination cycles, low ovarian reserve, endometriosis, recurrent miscarriage, genetic or chromosomal abnormalities transmissible to offspring and spontaneous or iatrogenic menopause, with a BMI of <30 kg/m² and without systemic illnesses that could be exacerbated during pregnancy or pose a risk to the patient in the event of gestation. In cases where there are uncertainties, as determined by the attending physician, or in recipients older than 45 years, a report from their primary care physician or responsible specialist certifying their good health for pregnancy will be required. To comprehensively study the clinical outcomes, we plan to retrospectively gather and analyze baseline information on recipients. The collected medical and gynecological data will include the following parameters: Age, BMI, uterine pathologies (endometriosis and adenomyosis, specifying the severity of these conditions), fibroids (type and measurement), immunological or hematological diseases, obstetrical history, endometrial thickness during the endometrial preparation phase and serum progesterone level prior to the transfer procedure.

For recipients with ovarian function, the hypophysis will be suppressed with GnRH agonists (Triptoreline, 3.75 mg, Decapeptyl 3.75 mg, Ipsen Pharma). This step will be omitted in patients with inactive ovaries. Subsequently, hormonal replacement therapy with transdermal estradiol or oral estradiol valerate will be initiated, following a step-up regimen, for a minimum of 10 days. An additional transvaginal ultrasound will be performed to assess endometrial thickness and pattern. If the physician deems it optimal, progesterone supplementation will be introduced (while continuing the estrogen regimen) either as 800 mg daily vaginal progesterone, as described previously by our group (15). Before the transfer, progesterone levels will be measured between days 3-5 of progesterone administration to customize the dosage for each patient.

In cases where a male partner is involved, a seminogram is conducted to evaluate basic sperm parameters. Based on the findings, the screening may be expanded to include additional tests for a more thorough analysis: Karyotype, DNA fragmentation test, testicular sonography (in instances where pathology is observed or suspected), Sperm Fluorescence *In Situ* Hybridization (FISH). If obstructive azoospermia is identified, a cystic fibrosis screening is conducted to assess the risk associated with this condition. Finally, we offer a genetic compatibility test, aiming to reduce the risk of recessive genetic diseases in the offspring.

### Study population

The study population comprises women undergoing controlled ovarian stimulation at Centers Accuna e Instituto Bernabeu Elche. Our study sample will be selected based on the following criteria:

Inclusion Criteria: Patients included in the study must meet the following inclusion criteria:

O Eligibility for participation in the Instituto Bernabeu’s oocyte donation program.O Age between 18 and 33 years.O BMI >18 and <30.O Antral follicle count >8 (combined count from both ovaries).O Presence of both ovaries.O Ability to participate and comply with the study protocol.O Proficiency in spoken and written Spanish.O Provided written informed consent.

Exclusion criteria: Patients meeting any of the following criteria will not be included in the study:

O Diagnosis of endometriosis (any stage).O Diagnosis of any ovarian tumor, whether benign or malignant.O Concurrent participation in another study.O Malabsorptive syndromes that may affect the efficacy of Seidigestan®, such as bariatric surgery, ulcerative colitis, or Crohn’s disease.O Patients with irregular menstrual cycles.O Patients with hypogonadotropic hypogonadism.O Received treatment with ovulation stimulators in the two months preceding the study.O Previously participated in the current study.

### Statistical analyses

#### Sample size

Considering an expected yield of 13.58 oocytes in the control group with a standard deviation of 6.997 (based on an internal study conducted within the clinic, encompassing all oocyte donor stimulations performed in 2021), and accepting an alpha risk of 0.05 and a beta risk of 0.20 in a one-sided test (with an 80% statistical power), a sample size of 136 patients (68 in each study group) is required to detect a minimum difference of 3 oocytes. Accounting for an estimated loss of 10%, a total sample size of 150 patients (75 per group) is needed.

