#### Data analysis

The descriptive statistical methods employed in this study will depend on the nature of the analyzed variables. For qualitative variables, the following descriptive statistics will be computed: frequency and percentage. Quantitative variables will be presented using measures of central tendency and dispersion.

For univariate statistical analysis of qualitative variables, the Chi-square test or Fisher’s exact test will be utilized. Normality of quantitative variables will be assessed through the Kolmogorov-Smirnov and Shapiro-Wilk tests, as well as visual examination of distribution (histogram, QQ-plot, and box plot). If the distribution is found to deviate from normality, logarithmic transformation of the variable will be applied. Subsequently, univariate analysis of quantitative variables will be performed using the t-Student test. Statistical significance will be considered at P < 0.05, and conclusions will be drawn with support from confidence intervals whenever applicable.

The primary objective of the study will be analyzed through an ANCOVA, using the treatment group assignment as a covariate, to determine whether there is an equivalent effect among subgroups or not.

For the analysis of secondary objectives, a multilevel model will be employed, considering the hierarchical structure of the data due to the fact that one donor may contribute to multiple recipients, as well as the number of cycles.

Data will be entered into a database within our department and analyzed using statistical software packages SPSS version 22.0 for Windows (SPSS Inc., Chicago, IL) and R version 4.2.2 for Windows (R Foundation for Statistical Computing, Vienna, Austria).

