#### Analysis of the primary outcome

The analysis of the primary variable will be presented as the mean number of oocytes along with its corresponding 95% confidence interval. Student’s t-test will be used to compare the mean number of oocytes between each group. A multivariate linear model will be adjusted for the number of oocytes, incorporating the group and potentially confounding variables. A variable selection process using stepwise selection based on the AIC (Akaike Information Criterion) will be conducted.

The primary analysis will be performed in the intention-to-treat (ITT) analysis population and will also be repeated in the per-protocol (PP) analysis population.

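### The trial is sized at one-sided alpha 0.05, but the only interval named for the primary outcome is a 95% CI; if that interval decides non-inferiority, power is about 70%, not 80%

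*Protocol article*

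**What the plan says.** The Study design section describes a non-inferiority comparison: "we have designed a prospective, randomized, non-inferiority comparative clinical trial". The Sample size section takes an "expected yield of 13.58 oocytes in the control group with a standard deviation of 6.997", sets the error rates by "accepting an alpha risk of 0.05 and a beta risk of 0.20 in a one-sided test (with an 80% statistical power"), and concludes that "a sample size of 136 patients (68 in each study group") "is required to detect a minimum difference of 3 oocytes". It then adds an allowance for losses: "Accounting for an estimated loss of 10%, a total sample size of 150 patients (75 per group) is needed".

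Under Analysis of the primary outcome, the result "will be presented as the mean number of oocytes along with its corresponding 95% confidence interval", and the arms are compared with Student's t-test. The general Data analysis section adds that "Statistical significance will be considered at P < 0.05" and that confidence intervals will support the conclusions where applicable. Neither analysis section gives the sidedness of a test, a 90% or one-sided interval, or a rule that sets an interval limit against 3 oocytes.

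**The concern.** A one-sided non-inferiority test at 0.05 is the same decision as checking whether the lower limit of a two-sided 90% CI for the difference lies above minus the margin. The lower limit of a two-sided 95% CI corresponds to a one-sided test at 0.025. The level used for sizing and the only interval level given for the primary outcome therefore belong to different tests, and nothing on the page says which one settles the question.

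Two things are at stake. One is the meaning of the 80% power: it holds under one rule and falls well short under the other. The other is the type I error rate of the headline conclusion, 5% or 2.5% one-sided. If the rule is settled only at reporting, it could be chosen with the results in view, in a trial where the two rules can point in opposite directions.

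**Working it through.** **Inputs.** SD 6.997, difference 3, one-sided alpha 0.05, power 80%, 68 evaluable and 75 randomized per arm, 10% loss (all from Sample size). Assumptions: the 3 oocytes serve as the non-inferiority margin (the text calls them a minimum difference to detect), the true difference is 0, and the SD is the same in both arms.

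**1. Reproduce the protocol's figure.** n per arm = 2 × [SD × (z for alpha + z for power) / 3]².
- One-sided 0.05: 2 × [6.997 × (1.645 + 0.842) / 3]² = 67.3, so 68 per arm and 136 in total. A noncentral-t calculation also gives 68.
- Losses: 136 × 1.10 = 149.6, so 150.

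The protocol's numbers reproduce.

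**2. Standard error of the difference.** SE = 6.997 × √(2/n).
- n = 68: SE = 1.200, and 3/SE = 2.500.
- n = 75: SE = 1.143, and 3/SE = 2.626.

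**3. Power under each rule.** Power = Φ(3/SE − z for alpha), with the noncentral-t value alongside.

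| Decision rule | 68 per arm | 75 per arm |
|---|---|---|
| One-sided 0.05 (90% CI limit) | Φ(2.500 − 1.645) = 80.4% (t: 80.0%) | Φ(2.626 − 1.645) = 83.7% (t: 83.4%) |
| One-sided 0.025 (95% CI limit) | Φ(2.500 − 1.960) = 70.5% (t: 69.9%) | Φ(2.626 − 1.960) = 74.7% (t: 74.2%) |

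After a 10% loss, 75 × 0.9 = 67.5 per arm remain, so the 68-per-arm column is the relevant one. The 75-per-arm column applies only with no losses.

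**4. Size needed for 80% at one-sided 0.025.** 2 × [6.997 × (1.960 + 0.842) / 3]² = 85.4, so 86 evaluable per arm (87 with the t distribution), against 68 planned.

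**5. Where the two rules disagree, at 68 per arm (134 degrees of freedom).**
- 90% CI half-width: 1.656 × 1.200 = 1.99. Non-inferiority is shown if the observed deficit is below 3 − 1.99 = 1.01.
- 95% CI half-width: 1.978 × 1.200 = 2.37. Non-inferiority is shown if the observed deficit is below 3 − 2.37 = 0.63.

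An observed deficit between about 0.63 and 1.01 mature oocytes is a success under the first rule and a failure under the second. If the arms are truly equal, that happens in about 80% − 70% = 10% of trials.

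**The case against.** The strongest reply is that the 95% CI is never made the decision criterion. The sentence is about presentation, and as worded the interval belongs to the mean number of oocytes, not to the between-group difference. The only test whose alpha and sidedness are both stated is the one in Sample size, and under it 80% is right. Reporting a 95% CI beside a one-sided 0.05 test is not inconsistent in itself. Using a 90% CI would follow the stated alpha, and the full protocol or analysis plan may say so.

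Most of this stands, and it rules out three stronger readings.
- A reader might infer that the true power is 70% or that the sample size contains an arithmetic error. The documents support neither: the calculation reproduces, and the lower figure depends on a decision rule that the article does not state.
- A reader might also take the P < 0.05 threshold as a contradiction of the one-sided alpha. It is not. The threshold carries no sidedness, and a one-sided test at alpha 0.05 is itself a P < 0.05 rule.
- A reader might expect covariate adjustment to make up the lost power. The article gives no figure from which a gain could be calculated, and its linear model selects covariates by stepwise AIC, so no credit can be taken for it.

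What the reply does not remove is the mismatch on the page. The article states an alpha for sizing and a confidence level for the primary outcome, and the two do not correspond. It lets intervals support conclusions, gives no other interval level, and does not carry the one-sided test into the analysis sections. A reader who applies those sections to a non-inferiority question would naturally use the 95% limit.

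**Conclusion.** The concern holds in conditional form. The 80% power is correct at one-sided 0.05 with 68 per arm. If the lower limit of the two-sided 95% CI for the difference decides non-inferiority, power is about 70% after planned losses and about 74% with none. The chance of missing non-inferiority when the arms are truly equal is then about 30% rather than 20%. These figures assume a margin of 3, a common SD of 6.997 and no true difference. The defect is a misalignment between sizing and analysis with the decision rule left open. It bears on the primary conclusion and is cheap to repair.

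**What to change.** Before any outcome data are seen, make the two sections agree by one of two routes.

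(a) Under Analysis of the primary outcome, state that non-inferiority is judged by the lower limit of the two-sided 90% CI for the between-group difference in mean mature oocytes (one-sided 0.05), compared with minus 3, and that the 95% CI is descriptive. Keep 80% power. The cost is that a one-sided type I error of 5%, less strict than 2.5%, becomes explicit.

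(b) Make the lower limit of the two-sided 95% CI for that difference decisive, and restate power in Sample size as about 70% with 68 evaluable per arm. The cost is a less favourable stated power.

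Each route takes a sentence or two and no added patients. Either way, the interval should be defined for the between-group difference, because the present wording attaches it to the mean.
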